#### Secondary outcome measures

Lysholm score at baseline, 3, 6, and 18 months after operationInternational Knee Documentation Committee (IKDC) score [23] at baseline, 3, 6, 12, and 18 months after operation. The IKDC scores range from 0–100 points and involves symptoms, sport activities, and function, with higher scores reflecting a better condition (knee function and symptoms)Visual Analog Scale (VAS) score [24] at baseline, 3, 6, 12, and 18 months after operation. The VAS is the most commonly used method to assess pain and consists of a 10-cm horizontal line with one end labeled as 0 cm representing “no pain” and the other end labeled as 10 cm representing “severe pain.” Patients will be instructed to make a mark on the line to indicate their pain intensity. The VAS scores range from 0–10 points, with 0 indicating no pain, 1–3 indicating mild pain, 4–6 indicating moderate pain, and 7–10 indicating severe painMRI examination to evaluate cartilage repair and regeneration at baseline, 3, 6, 12, and 18 months after operationAdverse events, such as fever, joint pain, swelling, effusion, and rejection after cartilage transplantation, will be observed at 3, 6, 12, and 18 months postoperatively. Common adverse events after microfractures include joint fever, joint pain, joint swelling, and effusion. All outcome evaluations will be performed independently and blindly by experienced evaluators

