### Sample size

Based on our previous experience [25] and pilot study results, we assumed that the therapeutic efficiency on full-thickness cartilage injury of the knee joint would be 78% for microfracture surgery and 97% for autologous, cell-derived, tissue-engineered cartilage transplantation. Considering *α* = 0.05 (two-sided), and power = 80%, the necessary sample size was calculated as *n* = 84. With a predicted dropout rate of 20%, the required sample size was calculated as *n* = 50 per group.

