### Statistical analysis

Data will be analyzed using SPSS19.0 software (IBM Corp., Armonk, NY, USA). A statistical significance level of 0.05 will be used. Normally distributed data will be expressed as the mean ± standard deviation, and non-normally distributed data will be expressed as the median, minimum, and maximum. Classified variables will be expressed as a number and percentage.

The analysis will be performed on the basis of the intent-to-treat principle. A full analysis set following the principle of intent-to-treat will consist of a data set for all patients who participated in the trial, regardless of compliance or withdrawal. For patients who are lost to follow-up, the missing data will be imputed by the last-observation-carried-forward method based on the final observed value.

Descriptive statistics will be used for baseline feature data. Pearson’s chi-squared test or Fisher’s exact test will be used for intergroup comparisons of categorical variables, such as curative outcomes and postoperative incidence of adverse events. For independent variables, such as IKDC score, VAS score, T2 value, and △*R1*, an independent sample *t* test or the Mann-Whitney *U* test will be used.

A multivariate logistic regression analysis model will be used to adjust for possible confounding variables such as age, sex, etiology, cartilage defect area, meniscus injury, course of disease, severity of cartilage injury, postoperative complications, and surgeon (experience).

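### IKDC and VAS are compared without adjusting for the baseline scores the trial already collects, which costs precision on two secondary endpoints

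*Protocol article*

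**What the plan says.** The Statistical analysis section groups the continuous secondary endpoints in one sentence that opens "For independent variables, such as IKDC score, VAS score, T2 value", adds ΔR1, and states that "an independent sample *t* test or the Mann-Whitney *U* test will be used". It names no covariate.

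The Secondary outcome measures section schedules both patient-reported scores before and after surgery. For pain it reads "Visual Analog Scale (VAS) score [24] at baseline, 3, 6, 12, and 18 months after operation", and IKDC has the same schedule.

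The Statistical analysis section gives baseline data one stated use: "Descriptive statistics will be used for baseline feature data". Adjustment appears once: "A multivariate logistic regression analysis model will be used to adjust for possible confounding variables". The examples of confounders that follow include neither baseline IKDC nor baseline VAS. No ANCOVA, change-from-baseline analysis or repeated-measures model is described.

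**The concern.** IKDC and VAS carry the first two secondary objectives, knee function and pain relief. A patient's score before surgery usually predicts part of the score afterwards. A two-sample test on the follow-up score leaves that predictable part in the error term, so the confidence interval is wider than it need be.

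There is also a conditional effect. The Randomization and blinding section describes no stratification on baseline score, so the arms will differ at baseline by chance, and part of that difference carries through to the unadjusted comparison. The one adjusted model cannot remove it: logistic regression needs a categorical outcome, whereas IKDC (0 to 100) and VAS (0 to 10) are assigned to two-sample tests as scores.

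The article names the tests itself, so this is a comment on a stated choice and not on detail left to an analysis plan that is not shown.

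**Working it through.** **Inputs**

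- Sample size: 50 per arm randomised (Study design; Sample size). The Sample size section's 84 before dropout gives 84/2 = 42 per arm.
- Two-sided α of 0.05 (Sample size). The 80% power used below is the protocol's power target for its binary primary outcome, borrowed here only as a reference point.
- Correlation r between a score at baseline and at follow-up: not in the documents. Assumed values are 0.3, 0.5 and 0.7.
- The protocol states no SD, effect size or power for IKDC or VAS, so it has no figure of its own to reproduce on this point.

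**Step 1: precision.** With equal SDs at baseline and follow-up, set to 1, the comparison of raw follow-up scores has relative variance 1 and ANCOVA has about 1 − r². The unadjusted standard error is therefore larger by the factor 1/√(1 − r²), and 50 patients per arm under ANCOVA are worth 50/(1 − r²) per arm unadjusted.

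**Step 2: power.** Take an effect that the unadjusted test detects with 80% power at 50 per arm: (1.960 + 0.842) × √(2/50) = 2.802 × 0.20 = 0.56 SD. Under ANCOVA the power is Φ(2.802/√(1 − r²) − 1.960).

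| Assumed r | Variance factor 1 − r² | Unadjusted SE larger by | Equivalent n per arm | ANCOVA power | Simulated ANCOVA power |
|---|---|---|---|---|---|
| 0.3 | 0.91 | 5% | 54.9 | 83.6% | 82.9% |
| 0.5 | 0.75 | 15% | 66.7 | 89.9% | 89.1% |
| 0.7 | 0.51 | 40% | 98.0 | 97.5% | 97.1% |

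The simulation used 20,000 runs per setting with normal data; the t test had power of about 79% throughout. At 42 per arm the variance factors are the same, and the equivalent sizes are 46.2, 56.0 and 82.4 per arm.

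**Step 3: chance imbalance.** At 50 per arm the difference in baseline means has standard deviation √(2/50) = 0.20 SD, with a 95% range of ±1.96 × 0.20 = ±0.39 SD. A fraction r of any such difference stays in the unadjusted estimate. An imbalance of 0.20 SD therefore shifts it by 0.3 × 0.20 = 0.06, 0.5 × 0.20 = 0.10 or 0.7 × 0.20 = 0.14 SD. In the simulation the mean error of the unadjusted estimate was about zero.

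**Step 4: if change scores were meant.** The text does not say whether raw or change scores are tested. A change score has relative variance 2(1 − r): 1.4, 1.0 and 0.6 for r = 0.3, 0.5 and 0.7. That is worse than the raw score when r is below 0.5. Against ANCOVA the ratio is 2(1 − r)/(1 − r²) = 2/(1 + r), or 1.54, 1.33 and 1.18. It exceeds 1 for every r below 1, so ANCOVA is at least as precise.

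**The case against.** The strongest reply is that nothing here is wrong. In a 1:1 randomised trial an unadjusted two-sample test is valid, the endpoints are secondary, and the primary conclusion and sample size rest on a responder proportion. That stands, and it limits the point to an improvement in efficiency.

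A second reply is that the size of the gain depends on an r that the documents do not give. That also stands. At r = 0.3 power rises only from 80% to about 84%, and the large gains need r near 0.7.

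A third is that a linear model on a bounded 0 to 10 scale brings assumptions that Mann-Whitney avoids. This is fair, and it is the reason to keep Mann-Whitney as a sensitivity analysis.

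Several stronger readings are tempting, and the documents do not support them:

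- *The IKDC and VAS results will be biased.* They will not be, on average. The imbalance is chance error in a given trial, and only the fraction r of it carries through.
- *The plan discards baseline altogether and treats visits as unrelated.* The text does not say whether change scores are used or how visits are combined, so neither can be asserted.
- *The same remedy extends to T2 and ΔR1, with normal control cartilage as covariate.* The captions of Figs. 5 and 6 present control-cartilage values as examples from one case each, and the T2 section schedules measurements of regenerative cartilage only. Routine collection is not established. Such values would also be measured after randomisation and could be affected by treatment, since only the experimental arm has a cartilage harvest and a second operation.
- *The Lysholm score should be modelled in the same way.* The protocol defines efficacy on that score as the proportion of excellent and good cases, so a model of its mean is a separate question.

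**Conclusion.** The point holds for IKDC and VAS as a worthwhile improvement to a stated method. The direction is certain for any non-zero correlation, apart from the negligible cost of estimating one extra coefficient. The size is not certain: variance falls by 9%, 25% or 49% at assumed r of 0.3, 0.5 or 0.7, with equal SDs at the two times and a roughly linear relation between baseline and follow-up. If change scores were intended, the wording should say so, and ANCOVA would still be the better choice. The primary comparison is unaffected.

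**What to change.** In the Statistical analysis section, take IKDC and VAS out of the two-sample-test sentence. State that each score, at 12 months and at each other postoperative visit, will be analysed by ANCOVA with treatment and the score's own baseline value, and that the adjusted mean difference will be reported with its 95% confidence interval. Keep Mann-Whitney as a sensitivity analysis, and say whether it is applied to raw or change scores.

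If a mixed model over visits is preferred, state that it replaces last-observation-carried-forward for these two scores, because the section currently imputes missing values by that rule.

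The cost is a few lines of analysis wording, to be settled before unblinding. No extra patients, visits or measurements are needed.

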### Study design

This prospective, single-blind, randomized controlled clinical trial will be conducted at the Institute of Orthopaedics, Chinese PLA General Hospital, China. The study design is compliant with the Standard Protocol Items: Recommendations for Interventional Trials (SPIRIT) Statement [20] (see Additional file 1). After providing informed consent, the potential patients with full-thickness cartilage injury of the knee joint will be screened according to the inclusion and exclusion criteria, and finally, 100 eligible patients will be randomly assigned to receive autologous-cell-derived tissue-engineered cartilage grafts (*n* = 50) or microfractures (*n* = 50). The primary outcome is therapeutic efficacy as assessed by the Lysholm score at 12 months postoperatively. The secondary outcomes are the IKDC score, Visual Analog Scale (VAS) score, and cartilage injury and repair as assessed by MRI as well as the incidence of postoperative adverse events (see the trial flow chart in Fig. 3). The Standard Protocol Items: Recommendations for Interventional Trials (SPIRIT) Figure is detailed in Fig. 4.

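### The supporting logistic model adjusts for postoperative complications, which arise after randomisation, and names about as many terms as there are expected failures

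*Protocol article*

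**What the plan says.** The Statistical analysis section of the protocol article compares curative outcomes between arms with Pearson's chi-squared or Fisher's exact test, and treats the postoperative incidence of adverse events in the same way. It then adds an adjusted analysis: "A multivariate logistic regression analysis model will be used to adjust for possible confounding variables such as age, sex, etiology". The list goes on to defect area, meniscus injury and course of disease, and ends with "severity of cartilage injury, postoperative complications, and surgeon (experience"). That makes nine named items. The section does not name the dependent variable. The natural reading is the efficacy rate defined under Primary outcome measure, where a Lysholm score of 60 or more is a success and 0 to 59 a failure.

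Under Sample size, the assumed efficacy rates "would be 78% for microfracture surgery and 97% for autologous, cell-derived, tissue-engineered cartilage transplantation". Under Study design, "100 eligible patients will be randomly assigned to receive autologous-cell-derived tissue-engineered cartilage grafts" or microfracture, 50 per arm.

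**The concern.** A confounder is a common cause of treatment and outcome. In a randomised trial, nothing that happens after surgery can be one. Postoperative complications may instead be a consequence of the allocated treatment, and the arms differ in exposure by design. The graft arm has two operations, a cartilage harvest and a cell-seeded implant. The control arm has arthroscopic debridement and microfracture. Rejection is named as an adverse event only after transplantation. Holding complications fixed takes out whatever part of the benefit or harm acts through them, so the adjusted odds ratio answers a different question from the intention-to-treat comparison that the section promises.

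The second issue is size. A logistic model draws its information mainly from the rarer outcome, here treatment failure. With about one failure per term, the coefficients are overfitted and unstable.

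At stake is the only adjusted efficacy analysis described. Its odds ratio could be reported as support for, or against, the main result while estimating something else, and imprecisely.

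**Working it through.** **Inputs.** Failure rates are 1 − 0.78 = 0.22 and 1 − 0.97 = 0.03 (Sample size). There are 50 per arm (Study design), 42 per arm from "the necessary sample size was calculated as *n* = 84", and 40 per arm if 20% of 50 drop out. The nine covariates come from Statistical analysis.

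**The plan's own figure.** For 78% vs 97%, two-sided 5% and 80% power, standard formulas give totals of 94 (pooled variance), 88 (unpooled), 80 (arcsine) and 114 (continuity-corrected). None gives 84. The present point does not depend on that figure, because the failure count is similar at 40, 42 or 50 per arm.

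**Roles given to complications.** In one section, postoperative adverse events are an outcome compared between arms and postoperative complications are a covariate. There is also possible overlap with the endpoint. The adverse event form records joint pain and joint swelling, and the Lysholm sheet gives 25 points to pain and 10 to swelling, so 35 of 100 points may measure what is also coded as a complication.

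**What conditioning does (illustration).** All rates and coefficients here are assumptions, not figures from the document. Let the log-odds of failure be −1.6 − 1.8 × graft + 1.5 × complication, with no unmeasured common cause. Failure risk without and with a complication is then 0.168 and 0.475 under microfracture, and 0.032 and 0.130 under graft. The adjusted odds ratio is exp(−1.8) = 0.165 throughout. The total-effect odds ratio depends on complication rates:

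| Complications, control vs graft | Failure risk, control | Failure risk, graft | Total-effect OR | Adjusted OR |
|---|---|---|---|---|
| 10% vs 30% | 0.9 × 0.168 + 0.1 × 0.475 = 0.199 | 0.7 × 0.032 + 0.3 × 0.130 = 0.062 | 0.265 | 0.165 |
| 20% vs 20% | 0.229 | 0.052 | 0.184 | 0.165 |
| 30% vs 10% | 0.260 | 0.042 | 0.125 | 0.165 |

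Adjustment flatters the graft in the first row and penalises it in the third. The middle row, with equal rates, shows that part of the shift is non-collapsibility of the odds ratio.

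**Failures per term.** Expected failures = n × 0.22 + n × 0.03. Terms = 9 + 1 = 10, counting each covariate as a single term.

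| n per arm | Expected failures | Per term | P(no graft failure) = 0.97^n |
|---|---|---|---|
| 50 | 11.0 + 1.5 = 12.5 | 1.25 | 21.8% |
| 42 | 9.24 + 1.26 = 10.5 | 1.05 | 27.8% |
| 40 | 8.8 + 1.2 = 10.0 | 1.0 | 29.6% |

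The central 90% range of the failure count is 7 to 18 at 50 per arm and 6 to 15 at 42. The plan carries the last observation forward, so dropouts stay in and may add failures. In the extreme case all of them fail: 10.5 + 16 = 26.5 (84 completers) or 10 + 20 = 30 (80 completers), which is 2.7 to 3.0 per term.

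**Estimability.** The last column is the chance of an empty failure cell in the graft arm, which makes the maximum-likelihood odds ratio infinite whatever else is in the model. In a 600-replicate simulation at 50 per arm, there was no usable estimate in 18% of trials with nine weak covariates and 21% with none. A separate simulation (1,000 trials per scenario, pure-noise covariates with assumed distributions) counted separation of any kind, including separation that leaves the treatment term finite. It gave 29% at 50 per arm and 36% at 42 with 10 terms, and 32% and 46% with 12 terms.

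**The case against.** The strongest reply is that this model is secondary. Efficacy is tested by an unadjusted chi-squared or Fisher test, the sample size rests on two proportions, and adverse events are compared separately. A reader might infer that the trial could hide a graft that fails through complications. The documents do not support that: the unadjusted test would still count those failures, and the adverse-event comparison would still show the complications. This part of the reply stands and limits the seriousness.

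A reader might also infer that the long covariate list is what makes the treatment effect inestimable. It is not the main cause. The empty-cell risk follows from a 97% success rate in 40 to 50 patients, and the 18% vs 21% comparison shows no added loss of usable estimates from the covariates. What the covariates add is overfitting and other forms of separation.

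The list is introduced as examples, and the final covariate set and method of entry may be left to an analysis plan not shown here. For that reason the absence of baseline Lysholm from the list is not an error, and nothing in the document shows how strong a predictor it is. The reply does not rescue postoperative complications, which the text expressly names as a variable to adjust for.

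**Conclusion.** The point holds for the supporting model. As written, its treatment odds ratio would not estimate the total intention-to-treat effect, because it conditions on a possible consequence of treatment. How far and in which direction it would be off cannot be stated from the document; the illustration shows shifts both ways under assumed rates. It would be wrong to infer that the adjustment must favour the graft.

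The model is also overfitted, at about 1.0 to 1.25 expected failures per term and at most about 3. This assumes that the dependent variable is the efficacy rate, that all nine named items are entered, and that the planned 78% and 97% hold. The 22% to 30% chance of no graft failures is a separate weakness of any maximum-likelihood logistic fit at these rates.

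The unadjusted comparison of the efficacy rate is unaffected. This should be fixed, but it does not threaten the main analysis.

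**What to change.** 1. Delete postoperative complications from the covariate list and report them only as a safety outcome.
2. Name the dependent variable and limit the adjusted model to a few prespecified baseline covariates, for example defect area, age and baseline Lysholm, fixed before unblinding.
3. Fit the model by Firth penalised likelihood or an exact method, and check that the named software can do it.

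All three are needed. Deleting complications alone leaves 9 terms, or 10.5/9 = 1.2 to 12.5/9 = 1.4 failures per term. Treatment plus one or two covariates (2 or 3 terms) gives 10.5/3 = 3.5 to 12.5/2 = 6.3. Three covariates (4 terms) give 10.5/4 = 2.6 to 12.5/4 = 3.1. Even then the chance of no graft failures remains, so step 3 still matters.

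The change is to analysis wording and needs no new data. The cost is that fewer variables are adjusted for in a secondary analysis. Modelling the Lysholm score as a continuous outcome would avoid the sparse failures but would change the estimand, so it is not part of this fix.

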### Ethics and dissemination

#### Ethical approval and informed consent

The study protocol was approved by the Ethics Committee of the PLA General Hospital (approval No. S2015-084-01). This trial will be conducted in accordance with the World Medical Association Declaration of Helsinki (revised version of Seoul, 2008) and international standards of Good Clinical Practice.

Prior to participation in the clinical trial, the participant or their family members, guardians, and/or legal representatives will be informed of the details of the clinical trial, including known, foreseeable risks, and possible adverse events. Then, the informed Consent Form will be given to the participant or their legal representative.

#### Dissemination

Without the written consent of the sponsor, the researcher will not disclose the data and other information relating to the clinical trial to a third party or for any other purpose. In any case that the researchers publish or reveal their research findings from the test products in the clinical trial, written consent must be given by the sponsor. If the researcher wishes to publish the information related to the trial the study, the original manuscript will be reviewed and approved by the sponsor at 60 days prior to submission or presentation. If there exists a problem related to the scientific findings, stringency, or compliance with laws and regulations, the sponsor will discuss these issues with the researchers. The sponsor cannot modify the scientific content of the manuscript and has no right to conceal relevant information. The authors’ signatures of the articles published in this study will be based on the author’s signature guidelines, such as the *Uniform Requirements for Manuscripts Submitted to Biomedical Journals*. The original raw images, data (including computer databases), and samples obtained during the trial will be published as supplementary information in peer-reviewed academic journals and published data will be released at www.figshare.com. The results of the trial will be disseminated through peer-reviewed publications and presentations at relevant conferences.

### Protocol amendments

All protocol modifications must be signed by the sponsor and dated, and then released. The modified protocol will be approved by the Ethics Committee prior to implementation. No program deviations should happen during the study. If so, appropriate measures should be taken immediately. Causes of a program deviation and its details should be recorded in a CRF and in the original eCRF. The program deviation table and CRF will be kept in the research unit and by the sponsor, respectively.

